### Treatment protocol

On the basis of the records in the ancient Traditional Chinese Medicine work *Huangdi Neijing*, treatment for flaccidity is aimed at the *yangming* meridian (ST). Acupoints in the stomach channel of foot-*Yangming* are the most involved ones, featuring a distribution around knees. *Futu* (ST32) and *Zusanli* (ST36) points on the stomach meridian of foot-*Yangming* are selected. Furthermore, according to the meridians and acupoints with opposite locations, combined with the principle of local acupoint selection [30], *Yinlingquan* (SP9) and *Yanglingquan* (GB34) are selected as a pair of acupoints located, respectively, at yin meridians and yang meridians with opposite locations; it can regulate yin and yang, qi, and blood with the selection of lesser points but with a better effect [22]. After discussion and consensus among acupuncture experts, the above four acupoints have been chosen for the study (Fig. 2).

**Fig. 2 Fig2:**
[figure not shown]
Acupoints of treatment, EA, and sham EA

Patients will stay in a relaxed and supine position before the onset of treatment. The acupuncturist will untie the elastic bandage that was fixed during the operation, so that the acupoints are exposed. The skin around the acupoints is sterilized with cotton dipped in 75% alcohol, and a sterile adhesive pad (10 mm in diameter, 5 mm thick) is pasted on each of the acupoints (Fig. 3). The sterile adhesive pad is made of a special sponge (Suzhou Medical Appliance Factory, China) with one sticky side which can be pasted on the skin. The role of the sterile rubber pad is to fix the location of acupoints and to ensure subject blinding. The participants in the three groups will receive a 30-min treatment on the first, second, and third day after operation by the same acupuncturist, three times per session. It will be difficult for them to ascertain which group they belong to.

**Fig. 3 Fig3:**
[figure not shown]
Needle and sham needle

#### Opposing EA group

The healthy side of the lower limbs will be treated with true EA while on the operated side sham EA will be used.

#### Operated side EA group

The operated side of the lower limbs will be treated with true EA while the healthy side will be treated with sham EA.

#### Sham EA group

Sham EA will be used on both the operated and healthy side.

The specific procedures of EA and sham EA are as follows (Fig. 2):

##### Electroacupuncture (EA)

Needles (0.30 mm in diameter, 40 mm in length, Hwato Brand, Suzhou Medical Appliance Factory, China) will be inserted vertically into the acupoints through the adhesive pads to a depth of 25–30 mm (Fig. 3). Acupuncturists will twist to achieve and enhance the sensation of needles inserted into the skin around acupoints, such as numbness, heaviness, aches, etc. (known as *De Qi*). Subsequent electrical stimulation (SDZ-V electroacupuncture apparatus, Huatuo brand, Suzhou Medical Appliance Factory, China) will be connected to each needle handle (a connecting wire connects a pair of acupoints, GB34 to ST32 and ST36 to SP9) and a continuous wave of 2 Hz frequency and an intensity of 1 mA will be maintained.

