### Study design

A randomized, controlled, three-arm, patient- and assessor-blinded trial will be conducted to compare the efficacy of two true EA groups (opposing EA and operated side EA) with a sham EA group (Fig. 1).

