##### Sham electroacupuncture (Sham EA)

The blunt needle (Fig. 3, 0.30 mm in diameter, 25 mm in length, Hwato Brand, Suzhou Medical Appliance Factory, China) will reach the skin through the adhesive pads without penetrating the skin. The needle handle is rotated three times to simulate the real acupuncture procedure. The sham electrical stimulation apparatus looks like the real one, but with the inner metal wire cut off so no current passes through the connecting wire between the two needle handle (GB34 to ST32 and ST36 to SP9); a continuous wave of 2 Hz frequency and an intensity of 1 mA is applied [31].

During the treatment, the needle handles are rotated on both sides three times per 5 min by acupuncturist.

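### The opening needle manipulation is open-ended at true points and fixed at three turns at sham points, so handling at the start of each session can differ between either true EA group and the sham group

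*Protocol article*

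**What the plan says.** The two opening steps are written out separately under Treatment protocol. Under Electroacupuncture (EA), once the needle is in, "Acupuncturists will twist to achieve and enhance the sensation of needles inserted into the skin around acupoints". The aim is De Qi, described there as feelings such as numbness, heaviness and aching. No count or duration ends the step. Under Sham electroacupuncture (Sham EA), a blunt needle touches the skin without piercing it, and "The needle handle is rotated three times to simulate the real acupuncture procedure". That step ends after a fixed count and has no sensation as its goal.

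The groups combine these steps by leg. In group A, "The healthy side of the lower limbs will be treated with true EA while on the operated side sham EA will be used". In group B, "The operated side of the lower limbs will be treated with true EA while the healthy side will be treated with sham EA". Group C has sham on both legs.

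Other parts of the session are matched: "During the treatment, the needle handles are rotated on both sides three times per 5 min by acupuncturist", and "The participants in the three groups will receive a 30-min treatment on the first, second, and third day after operation by the same acupuncturist".

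Study design describes a "randomized, controlled, three-arm, patient- and assessor-blinded trial". It also lets the treating operator, and nobody else, open the envelope holding the group code, so the person doing the manipulation knows the group. Of the patients, Treatment protocol says: "It will be difficult for them to ascertain which group they belong to". Under Primary outcome measurement, patients mark their own pain on the VAS directly after treatment on days 1 to 3, and again on days 5, 7 and 10.

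**The concern.** A sham group should receive everything the true groups receive except the component under test. Here one element differs by group in the protocol's own wording: how long and to what end the acupuncturist works the needle at the start of a session. Because that person is unblinded, the difference runs systematically with allocation. It does not average out over practitioners either, since the article foresees the same acupuncturist for all three groups.

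At stake is how a difference between a true group and sham would be read. The primary outcome is a patient-marked score, and such scores can respond to attention and expectation as well as to treatment. If patients in A and B are handled for longer, or spoken to differently during that step, part of an A-versus-C or B-versus-C difference could come from the encounter rather than from EA. This is separate from whether the needles and stimulator look alike. The pad, the blunt needle and the look-alike device hide appearance; they do not equalise what the acupuncturist does.

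**Working it through.** The article states no figure on this point, so the check compares the passages and counts.

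**Inputs**

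- 4 acupoints per leg and 2 legs (Abstract and Treatment protocol).
- 3 sessions, one on each of days 1, 2 and 3 (Abstract and Table 1), each of 30 min (Treatment protocol). I assume one 30-min treatment per day.
- Rotation during the session: three times per 5 min on both sides. The sentence stands under the sham heading but refers to both sides, so I apply it to all groups.
- Planning means on the VAS: 37.0 for opposing EA and 46.9 for sham EA (Sample size).

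**Step 1: what is matched.** Rotations during the session are 30 / 5 × 3 = 18 per needle, the same for true and sham needles in all three groups. Session length, acupoints and adhesive pads are also the same.

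**Step 2: what is not matched.**

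| | True point | Sham point |
|---|---|---|
| Opening manipulation | Twisting directed at De Qi | Three rotations |
| What ends it | No count or time given | The count |
| Sensation sought | Yes | No |

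**Step 3: how it falls by group.** Each patient has 8 × 3 = 24 point-treatments.

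| Group | Open-ended opening | Fixed opening |
|---|---|---|
| A, opposing EA | 4 × 3 = 12 | 12 |
| B, operated side EA | 4 × 3 = 12 | 12 |
| C, sham EA | 0 | 24 |

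**Step 4: difference in handling time.** Let T be the mean opening time at a true point and S that at a sham point. Total opening time over three sessions is 12T + 12S in A, 12T + 12S in B, and 24S in C. Hence:

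- A − C = 12(T − S)
- B − C = 12(T − S)
- A − B = 0

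Each second by which T exceeds S adds 12 seconds per patient over the course. The article gives neither T nor S.

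**Step 5: scale on the outcome.** The planning difference is 46.9 − 37.0 = 9.9 mm, so a shift of 1 mm from unequal handling would be 1 / 9.9, or about 10% of it. This only shows the scale. Nothing in the document says whether such a shift occurs or how large it would be.

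**The case against.** The case on the other side has real force, and several stronger readings fail.

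- **Prompting.** A reader might infer that the acupuncturist twists until the patient reports De Qi, and so questions patients at true points only. De Qi is felt by the patient, so this is plausible, but the article describes no questioning or feedback during treatment at either kind of point. The supported statement is that any exchange during this step is not matched in the text.
- **A sham that controls for nothing.** This is too broad. Points, pads, acupuncturist, session length and the 18 rotations per needle are equal, and sham has its own opening rotation.
- **Bias in A versus B.** Each group has one true and one sham leg, so total handling is balanced.
- **A stated size of bias.** A reader might assume a shift of a few millimetres, say 2 to 5 mm, but no figure in the document supports it. That the bias would favour the true groups is a reasonable expectation, not something shown. The VAS also follows the end of a 30-min session, whereas the unmatched step is at its start.
- **De Qi is part of the treatment.** This stands: the sensation belongs to true EA as described and is partly the intended contrast. The unequal handling time around it need not be.
- **A journal article leaves operating detail to the full protocol.** This would answer a complaint that a script is missing. It does not answer the point here, because both opening steps are printed and they differ.
- **The blinding questionnaire covers it.** After the third treatment every group rates needle sensation and says which leg was needled. That may reveal a perceived difference, but it does not measure handling time.

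**Conclusion.** The concern holds in a limited form. The opening manipulation is goal-directed and open-ended at true points and fixed at three turns at sham points. It is delivered by an acupuncturist who knows the group, at 12 of 24 point-treatments per patient in A and B and at none in C. Handling time and any accompanying exchange can therefore differ in A versus C and B versus C, with a patient-marked primary outcome read after each session. A versus B is not affected in total handling.

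The conclusion rests on the printed wording of the two procedures and on one 30-min treatment per day. The excess time, 12(T − S), and any effect on the VAS cannot be derived from the document; if T and S are in practice about equal, the problem largely disappears. It is a modest performance-bias point that can be closed cheaply. It does not invalidate the sham and does not bear on the sample size.

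**What to change.** 1. Leave the true EA procedure as it is.
2. Have the simulated opening manipulation at sham points last about as long as that at true points. Group C has no true leg to time against, so take the reference from times recorded on true legs.
3. Use the same short, neutral wording to every patient in all three groups during the opening step.
4. Record opening manipulation time per leg at each session, and report it by group so that equality can be checked.

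Two additions are better avoided. Asking about sensation at all eight points could invite patients to compare one leg with the other and weaken the masking. Capping the time allowed for De Qi would alter the active treatment.

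The cost is a slightly longer sham step and one more item on the case report form. Under Data management, protocol changes go to the ethics committee, so a short amendment is needed. For sessions already delivered without timing, the unmatched step should be reported as a limitation of the comparisons with sham.

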##### Sham electroacupuncture (Sham EA)

The blunt needle (Fig. 3, 0.30 mm in diameter, 25 mm in length, Hwato Brand, Suzhou Medical Appliance Factory, China) will reach the skin through the adhesive pads without penetrating the skin. The needle handle is rotated three times to simulate the real acupuncture procedure. The sham electrical stimulation apparatus looks like the real one, but with the inner metal wire cut off so no current passes through the connecting wire between the two needle handle (GB34 to ST32 and ST36 to SP9); a continuous wave of 2 Hz frequency and an intensity of 1 mA is applied [31].

During the treatment, the needle handles are rotated on both sides three times per 5 min by acupuncturist.

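### The stated needle and pad dimensions leave the sham needle 5–15 mm higher than the real one, a possible visual cue in groups A and B only that may threaten patient blinding unless the view is blocked

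*Protocol article*

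**What the plan says.** All statements are in the protocol article.

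- **Pad** (Treatment protocol, text after Fig. 2): "a sterile adhesive pad (10 mm in diameter, 5 mm thick) is pasted on each of the acupoints". Its purpose is also given: "The role of the sterile rubber pad is to fix the location of acupoints and to ensure subject blinding". The paragraph ends by saying of the patients: "It will be difficult for them to ascertain which group they belong to".
- **Real needle** (Electroacupuncture): "Needles (0.30 mm in diameter, 40 mm in length, Hwato Brand, Suzhou Medical Appliance Factory, China"), which "will be inserted vertically into the acupoints through the adhesive pads to a depth of 25–30 mm". The surface from which depth is counted, skin or pad top, is not stated.
- **Sham needle** (Sham electroacupuncture): a blunt needle, "0.30 mm in diameter, 25 mm in length, Hwato Brand, Suzhou Medical Appliance Factory, China) will reach the skin through the adhesive pads without penetrating" it. The apparatus is a look-alike with its inner wire cut, and handles on both sides are rotated during treatment.
- **Group A** (Opposing EA group) is described thus: "The healthy side of the lower limbs will be treated with true EA while on the operated side sham EA will be used".
- **Group B** (Operated side EA group) is described thus: "The operated side of the lower limbs will be treated with true EA while the healthy side will be treated with sham EA".
- **Group C** (Sham EA group): sham on both legs.
- **Outcomes** (Primary outcome measurement): patients mark the VAS themselves, immediately after each of the three treatments and again on days 5, 7 and 10. Additional PCA doses are the second primary component.
- **Check on masking** (Assessment of the subject blinding success rate for acupuncture): after the third treatment patients are asked, among other things, which leg they think was needled.

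**The concern.** The trial is declared patient-blinded, and the article names the pad as the means. A pad can hide whether the tip enters the skin. It cannot hide how much of the needle stands above it, and the two needle types differ in both length and depth.

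In most sham acupuncture trials a patient sees one needle type and has nothing to compare it with. Here the comparison is built into the two true arms: real needles on one leg and sham needles on the other, at the same four acupoints, for 30 minutes on three days. In group C the two legs look alike. If the difference can be seen, the cue is present in A and B and absent in C.

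Both primary components depend on the patient, who marks the VAS and triggers the extra PCA doses. Any expectation that the cue created would run along the A–C and B–C contrasts, the very contrasts for which the sham is there to hold expectation equal.

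**Working it through.** The article states no protruding length, so there is no figure of its own to reproduce. The check is simple geometry.

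**Inputs**
- Real needle length 40 mm, depth d = 25 to 30 mm (Electroacupuncture)
- Sham needle length 25 mm, depth into the skin 0 mm (Sham electroacupuncture)
- Pad thickness p = 5 mm, the same at every acupoint (Treatment protocol)

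**Length above the pad**
- Sham: 25 − p = 25 − 5 = 20 mm.
- Real, depth counted from the skin: 40 − p − d, which is 40 − 5 − 30 = 5 mm to 40 − 5 − 25 = 10 mm.
- Real, depth counted from the pad top: 40 − d, which is 40 − 30 = 10 mm to 40 − 25 = 15 mm.

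**Difference, sham minus real**
- Depth from the skin: 20 − 10 = 10 mm to 20 − 5 = 15 mm.
- Depth from the pad top: 20 − 15 = 5 mm to 20 − 10 = 10 mm.
- Over both readings: 5 to 15 mm, always with the sham higher.

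**How far this depends on the unknowns**
- *Pad compression.* With depth from the skin, the difference is (25 − p) − (40 − p − d) = d − 15, so p cancels and it stays at 10–15 mm. For example, at p = 3 mm the sham stands at 22 mm and the real needle at 7–12 mm. With depth from the pad top, the difference is d − 15 − p: 5–10 mm at p = 5 and 10–15 mm at p = 0. Compression does not take it below 5 mm.
- *Handles.* If the stated lengths include handles of both needles, the difference is unchanged. If they are shaft lengths and the handles are equal, it is again unchanged. A sham handle shorter by 5–15 mm would equalise total height, but the handles would then differ. Handle lengths are not given.
- *Retraction.* A sham needle sliding into its handle would change the result. The text does not describe one, and Fig. 3 is not shown.

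**Pattern by arm**
- A: operated leg 20 mm (sham), healthy leg 5–15 mm (real)
- B: operated leg 5–15 mm (real), healthy leg 20 mm (sham)
- C: 20 mm on both legs

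**The case against.** A reader might infer that patients can tell their legs apart and know which one is truly needled. The documents do not support that, for four reasons.

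- *Line of sight.* The patient is supine and the bandage is untied to expose the acupoints. Nothing is said about whether the patient can see both knees. The article mentions no drape, but room set-up is a detail that a condensed article may leave to the full protocol, so its absence proves nothing.
- *What is seen.* The visible object is shaft plus handle plus wire, so a ratio of bare shaft lengths would exaggerate the contrast. Figs 2 and 3, which would settle much of this, are not shown.
- *Which leg is real.* Noticing a difference is not the same as knowing that the taller needle is the sham. The documents at hand do not show what patients are told about the needles.
- *Reach.* A reader might also infer that every A–C and B–C comparison is confounded. Knee circumference is a physical measurement, range of motion is read with a protractor, and outcome assessment is by researchers unaware of allocation. The resting VAS at 6 hours precedes the first treatment.

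The article also takes masking seriously: pads at every point, rotation of the handles on both sides, a look-alike apparatus, and a questionnaire that asks about the needled leg.

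All of this stands, and it reduces the point from a demonstrated failure of blinding to a threat. It does not remove the mismatch: no reading of the stated depth gives equal protrusion, and the pad, the named safeguard, does not cover it. The questionnaire comes after the third treatment, so it could detect a failure but not prevent one.

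**Conclusion.** The point holds as a threat to blinding. By the article's own dimensions the sham needle stands 5–15 mm higher above the pad than the real one (10–15 mm if depth is counted from the skin, 5–10 mm if from the pad top). This assumes similar handles and a sham needle that does not retract. The asymmetry lies between the legs in groups A and B and is absent in group C.

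If patients can see both legs, it may reveal a difference in the true arms only, and so puts at risk the blinding of the VAS and PCA demand in the A–C and B–C comparisons. Whether patients do see it, and whether they would read it correctly, cannot be settled from the article. The size and direction of any bias cannot be derived from it either. What can be said is that the pad alone does not support the statement that it ensures subject blinding. This is worth a cheap correction.

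**What to change.** 1. In all three arms, block the patient's view of both legs with the same drape from before needle placement until removal. If this is already done, one sentence saying so answers most of the point.
2. State from which surface the real needle's depth is counted, and choose a sham needle whose protrusion falls within the range left by the real one. The sham length equals the target protrusion plus the 5 mm pad: 10–15 mm for a protrusion of 5–10 mm (depth from the skin), or 15–20 mm for a protrusion of 10–15 mm (depth from the pad top). This again assumes similar handles. The true EA procedure stays as it is.
3. Bring the statement on the pad's role into line with whatever is adopted.

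The cost is a drape and the sourcing of a different blunt needle length, whose availability would have to be confirmed. No patients, visits or staff are added. Because the real depth varies by 5 mm, the match can only be approximate: a sham set at the middle of the range could still differ by 5 / 2 = 2.5 mm. The drape is therefore the main safeguard. It removes the visual cue only, so the blinding questionnaire should stay.

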### Outcome measures

#### Primary outcome measurement

The main evaluation criterion is pain, which is divided into two parts.

The first part is a visual analogue scale (VAS). The assessment schedule is shown in Table 1. Independent assessors who are not involved in acupuncture treatments will perform the VAS assessments (asking subjects to indicate the intensity of pain at the most painful points while resting and walking). The 0–100 mm VAS is used to evaluate pain intensity, wherein 0 mm denotes painless and 100 mm represents the most intolerable pain [32]. It allows patients to mark their own feelings on the scale as the evaluation score of pain. In addition to evaluating resting pain at 6 h after the operation, the pain in both the resting and active state is measured immediately after treatment on the first to third days after the operation, and assessed at follow-up on the fifth, seventh, and tenth days after the operation.

**Table 1 Tab1:** Schedule of trial enrollment, interventions, and assessments

Items	Enrollment (pre-operative)	Allocation (baseline)	Treatment (post-operative)				Follow-up		
Time point (hour/day)	-1	-1	6 h	1d	2d	3d	5d	7d	10d
Treatment sessions (n)	–	–		1	2	3			
Informed consent	√								
Assessment of eligibility	√								
VAS (resting)		√	√	√	√	√	√	√	√
VAS (active)		√		√	√	√	√	√	√
Additional dose released by PCA pump					√				
HSS score		√				√			√
HAMA score		√				√			√
AROM		√				√	√	√	√
PROM		√				√	√	√	√
COK				√		√	√	√	√
Discomfort and acceptance of EA				√	√	√			
Assessment of blinding method						√			
Postoperative complications and adverse events				√	√	√			

*VAS* Visual Analogue Score, *PCA* patient controlled analgesia, *HSS* hospital for special surgery, *HAMA* Hamilton Anxiety Scale, *COK* circumference of knee, *AROM* active range of motion, *PROM* passive range of motion

The second part is to record any additional doses from the patient-controlled analgesic pump after the operation, and to evaluate it uniformly on the second day after the operation (at 24 h after the first treatment).

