## Abstract

**Background:**

This randomized controlled clinical trial aims to evaluate the efficacy and safety of opposing needling in patients undergoing unilateral total knee arthroplasty (TKA). Opposing needling is one of the special needling methods used in acupuncture and moxibustion therapy. It involves needling acupoints on the contralateral side for pain management. Although, opposing needling is used for pain management in clinics, evidence to support its effectiveness as an analgesic after total knee arthroplasty is scant. We designed a randomized controlled clinical trial to evaluate efficacy and safety of opposing electroacupuncture (EA) in alleviating pain associated with unilateral total knee arthroplasty.

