**Methods/design:**

This is a protocol for a randomized controlled patient- and assessor-blinded trial with three parallel arms (A, opposing EA; B, operated side EA; C, sham EA). *Yinlingquan* (SP9), *Yanglingquan* (GB34), *Futu* (ST32), and *Zusanli* (ST36) acupoints are selected for all three groups. In group A, the healthy side will be treated with EA, while the operated side will be administered sham EA. In group B, the operated side will be treated with EA while on the healthy side sham EA will be used. For group C, sham EA will be used on both sides. All patients in the three groups will receive treatment once a day for 3 days. The post-operative pain measured using a visual analogue scale score (including pain while resting and being active) and the additional dose of the patient-controlled analgesic pump after operation will be recorded as the primary outcomes. Secondary outcomes such as knee function and swelling, range of motion (including active and passive range of motion), post-operative anxiety, and acupuncture tolerance will also be assessed.

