### Eligibility

#### Inclusion criteria

Subjects are eligible to participate if they meet the following criteria: (1) aged 40 to 75 years; (2) meet the Clinical Classification Criteria for Osteoarthritis of the Knee as recommended by the American College of Rheumatology; (3) undergoing unilateral TKA under general anesthesia during hospitalization without surgical contraindications; (4) American Society of Anesthesiologists (ASA) grade I or II [29].

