### EA safety and adverse events

Although acupuncture has been deemed a safe and reliable therapy, its adverse effects and complications associated should raise concerns [12]. Clinically, the incidence of minor adverse events related to acupuncture may be higher, such as pain, local infection, fatigue, local hematoma, subcutaneous hemorrhage, etc. [38, 39]. Some of these might be avoidable [40]. During the treatment period, acupuncturists will strictly abide by the operating rules of electroacupuncture [41]. All acupoints are around the knee joint(s). Acupuncture insertion is in the superficial or subcutaneous regions. Occasionally, there will be a small amount of bleeding or bruising. The bleeding can be arrested by pressing with sterile cotton swabs or cotton balls. The bruising usually disappears within 2–3 days [32].

In this study, during the entire clinical trial, observers who are also blinded to group allocation will record the adverse events (AEs) related to acupuncture treatment in detail and enumerate the incidences. AEs will be managed by acupuncturists and relevant clinical experts within 24 h. Any adverse event, whether related to treatment or not, is reported by the participants and practitioners at every visit.

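### The primary VAS question is not anchored to the operated knee, in a trial whose arms differ in which leg receives true EA

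*Protocol article*

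**What the plan says.** All references are to the Protocol article.

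- **Question put to patients** (Primary outcome measurement): the assessor works by "asking subjects to indicate the intensity of pain at the most painful points while resting and walking". No other section limits the VAS to a particular knee.
- **Target** (Abstract, Background): the trial is to "evaluate efficacy and safety of opposing electroacupuncture (EA) in alleviating pain associated with unilateral total knee arthroplasty". The abstract's methods paragraph likewise calls the VAS outcome post-operative pain.
- **Site of true EA** (Opposing EA group), as stated for that arm: "The healthy side of the lower limbs will be treated with true EA while on the operated side sham EA will be used". The operated side EA group is the mirror image, and the sham group gets sham on both legs. The section on EA safety places all acupoints around the knee.
- **Eligibility** (Inclusion criteria): patients must "meet the Clinical Classification Criteria for Osteoarthritis of the Knee as recommended by the American College of Rheumatology" and be "undergoing unilateral TKA under general anesthesia during hospitalization without surgical contraindications". Neither the inclusion nor the exclusion criteria mention pain or osteoarthritis in the other knee. The Discussion explains the healthy leg simply as the unoperated one.
- **Timing** (Primary outcome measurement, Table 1): VAS at baseline, at 6 h (rest only), immediately after each treatment on days 1 to 3, and on days 5, 7 and 10.

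**The concern.** In most analgesic trials a question about the worst pain anywhere adds similar noise to every arm. Here the randomised factor is the leg that gets active treatment, so pain site and allocation are linked by design. The other leg can enter the score by two routes.

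1. *Relief.* A patient with two osteoarthritic knees is eligible. If the other knee is the worst point, true EA around it in the opposing arm may lower the score by acting locally. That would look like analgesia for the operated knee by contralateral needling, which is the claim under test.
2. *Ache.* True EA goes 25 to 30 mm deep and is meant to evoke sensations that include aches; sham does not penetrate the skin. The safety section says: "Clinically, the incidence of minor adverse events related to acupuncture may be higher, such as pain, local infection, fatigue, local hematoma". On days 1 to 3 such an ache could raise the score. It would come from the other leg in the opposing arm and from the operated leg in the operated side arm, with no penetrating needle in the sham arm.

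The VAS as described does not record the site of the pain, so a later analysis could not separate these cases from relief of the operated knee.

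**Working it through.** **The plan's own figure.** The Sample size section gives mean VAS 46.9 (SD 12.5) for sham and 37.0 (SD 22.6) for opposing EA. The planned difference is 46.9 − 37.0 = 9.9 mm. This is the yardstick below.

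**What the documents do not give.** There is no figure for pain in the other knee, for how often it is the worst site, or for the effect of local EA on it. What follows illustrates size under assumptions.

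**Model.**
- Score = max(operated-knee pain, other-knee pain), since the question asks for the worst point.
- The two pains are taken as independent normal variables, clipped to 0–100, with 2,000,000 draws.
- Operated knee: mean 46.9, with no treatment effect on it.
- SD at both sites: √((22.6² + 12.5²)/2) = √((510.76 + 156.25)/2) = √333.5 = 18.26.
- Assumed: other-knee mean 10 to 40 mm (before clipping) and local reduction 5 to 20 mm.
- Apparent effect = mean of max(operated, other) − max(operated, other − reduction).

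| Other-knee mean (assumed) | Other knee is worst | Shift, 5 mm relief | Shift, 10 mm relief | Shift, 20 mm relief |
|---|---|---|---|---|
| 10 mm | 8% | 0.3 mm | 0.5 mm | 0.8 mm |
| 20 mm | 15% | 0.6 mm | 1.1 mm | 1.6 mm |
| 30 mm | 26% | 1.1 mm | 2.0 mm | 3.1 mm |
| 40 mm | 39% | 1.8 mm | 3.2 mm | 5.2 mm |

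The range is 0.3 to 5.2 mm, or 0.3/9.9 = 3% to 5.2/9.9 = 53% of the planned difference. The top value needs an other knee averaging 40 mm against 46.9 mm in the operated knee, together with 20 mm of local relief.

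**Why share times effect is too simple.** Multiplying the share of patients by the local effect overstates the shift. Once the other knee drops below the operated knee, the patient scores the operated knee and the fall stops there. At an other-knee mean of 30 mm and 20 mm of relief, the product is 0.256 × 20 = 5.1 mm, while the model gives 3.1 mm.

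**Direction.** The table covers relief only. Needling ache in the opposing arm on days 1 to 3 would raise the score and work against that arm. The documents give no size for it, so the net sign cannot be derived.

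**The case against.** The strongest reply is that the target is clear from context. The abstract calls the outcome post-operative pain and the aim is pain from TKA, so the worst point may simply mean the worst spot of the surgical pain. The exact item wording belongs in the CRF or assessor instructions, which are not shown. This lowers the severity but does not dispose of the point: the article does state a site rule, and the rule names no limb.

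Several further objections stand.

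- The other knee counts only when it hurts at least as much as a freshly operated one. Nothing in the documents shows that this is common within 10 days of surgery.
- Timing limits the relief route. Baseline precedes treatment, and EA ends on day 3, so an effect on days 5 to 10 would need lasting local relief in the other knee.
- The other primary measure, additional PCA doses, does not use this question.

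A reader might infer that opposing EA versus sham is biased in favour of opposing EA, or that opposing versus operated side EA compares pain at different sites. The documents support neither. Relief and ache run in opposite directions. Every arm is asked the same question, and randomisation balances the worst site before treatment in expectation.

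**Conclusion.** The point holds as a defect in the wording of a primary outcome. The VAS question as stated is not tied to the operated knee, a painful other knee is not excluded, and the arms differ in which leg gets true EA. Pain in the non-operated leg can therefore enter the score differently by arm.

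Neither the size nor the sign of a net bias is shown. The relief effect of about 0.3 to 5 mm rests on assumed other-knee pain, assumed local relief, independence of the two knees and no effect on the operated knee. It stays well below 9.9 mm unless the other knee is nearly as painful as the operated one. Severity is minor to moderate. The change is worth making because it is nearly free and the ambiguity could not be resolved after data collection.

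**What to change.** Word the VAS instruction at every time point, baseline included, as *pain in the operated knee, at rest / when walking* (rest only at 6 h), and state this in the Primary outcome measurement section. If the CRF already says so, bring the article's description into line with it.

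Do not add a clause that excludes soreness at needle sites. It has no meaning at baseline or 6 h. It is hard to apply in the operated side arm, where the needles surround the operated knee, and it could draw patients' attention to which leg was needled.

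Optionally, record pain in the other knee as a separate, non-primary item, to show whether local relief or ache there is present and differs by arm.

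Cost: one line in the VAS instruction and CRF, plus a note in assessor training. The optional item adds seconds per assessment. The sample size and visit schedule do not change.
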